### The intervention: BOOST-A™

Using the transition planning objectives for adolescents on the autism spectrum (Fig. 1), the primary researcher (MH) developed the BOOST-A™. The BOOST-A™ was written in plain language at a year five reading level. This reading level has been recommended as being appropriate to disseminate health communication materials to the community, including low-literacy readers [43]. Feedback was obtained by a community reference group comprised of young people on the autism spectrum, parents and professionals throughout the development of the BOOST-A™ to ensure it met the needs of adolescents on the autism spectrum.

The BOOST-A™ is delivered in four online modules with an introduction via a website that requires a login. Table 1 shows the objectives addressed in each module. Each of the BOOST-A™ modules contains interactive cartoon videos that explain to the adolescent the overall purpose of transition planning, as well as the aim of each module. This links back to the guiding ideal identified in the needs assessment of ‘promote the big picture’.

**Table 1 Tab1:** BOOST-A™ overview

Module	Description	Who and where	Objectives addressed
Introduction	Information about the process and what to expect in the program, and why it is important to engage in transition planning from an early age	Adolescent and their parent/s at home	1, 2, 4
1. About Me	Six activities to identify the adolescent’s interests, strengths, work preferences, training goals, life skills and learning style	Adolescent and their parent/s at home	2, 3, 4, 5
2. My Team	Guides how to identify a team of people to support the adolescent in their transition planning, and how to book the first team meeting. Adolescents choose how they want to get involved in the team meetings, with graded prompts provided	Adolescent and their parent/s at home	2, 4, 5
3. First Meeting	Guides the first meeting; when the team are provided with recommendations for job areas and goals based on the adolescent’s strengths and evidence from the literature	Adolescent, their parent/s and their team at the first meeting	2, 3, 4, 5
4. My Progress	Guides the progress meetings; when the team review how the adolescent’s goals are progressing; and discuss positive learning experiences	Adolescent, their parent/s and their team at subsequent team meetings	2, 3, 4, 5

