### Trial design and procedures

A controlled clinical trial [47] will be used to determine the effectiveness of the BOOST-A™ in improving the self-determination of adolescents on the autism spectrum; and in improving their outcomes of quality of life, access to environmental supports, and career planning skills. The trial will be a cluster group, two-arm, superiority trial with 1:1 allocation ratio. The trial will aim to detect any difference in these outcomes between participants in the intervention group (BOOST-A™) and a control group. Figure 2 shows the schedule of enrolment, intervention, and assessment for the trial. Participants in the intervention group will complete the BOOST-A™ at home and/or at school. Participants will complete the BOOST-A™ over a period of 12 months. This timeframe was chosen to ensure the participants have adequate time to complete all four modules, including the initial team meeting and at least one review meeting. Adherence will be monitored via website analytics, including number of modules completed and number of logins to the BOOST-A™ website. Participants allocated to the control group will participate in the existing post-school planning process used at their school (regular practice).

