##### Treatment allocation

Following initial screening, potential participants will be allocated to either the intervention or control group according to the order in which they register interest. The first participant will be allocated to a group based on a coin toss completed by a researcher who will not be directly involved in liaising with participants. The exception to this allocation scheme is that if a newly enrolled participant is attending a school that a previously or currently enrolled trial participant attends, then the newly enrolled participant will be allocated to the same treatment group as the previous student. The reason for this is to reduce the risk of contamination, since school staff will be involved in administering the intervention. Participants will be blinded to their treatment; however, non-blinded allocation and lack of randomization could introduce potential bias. Once allocated to a group, participants will be sent the participant information and consent form. Forms for the intervention group will differ slightly from those for the control group, as they will contain information about the BOOST-A™, to ensure blinding to treatment is maintained. Participants who provide written consent will then be assigned a unique participant identification number. A strength of the trial is that the BOOST-A™ will be administered by parents and professionals who are not a part of the research team, thereby minimizing researcher bias. In addition, the primary researcher will have minimal information about the participants at time of randomization.

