#### Outcome measures

Outcome measures were determined based on a literature review of all suitable measures and their psychometric properties. Outcome measures were chosen based on the transition planning objectives for adolescents with autism, as identified in the needs assessment (Fig. 1). For example, fostering self-determination through high expectations is linked to the outcome of self-determination, and having a strong transition team is linked to measuring learning climate. As the BOOST-A™ was developed based on these objectives, the aim was to determine if it was effective in bringing about change in these areas. Particular emphasis was placed on each measure’s sensitivity to detect change. The outcome measures are all self-report, eliminating the risk of assessor bias. All of the outcome measures were trialed in Pilot A with six adolescents on the autism spectrum and their parents to ensure they were appropriate for use with these groups. Modifications were required for two of the questionnaires, as described below.

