### Ethics, consent and permissions

Ethics approval to conduct this trial has been obtained from Curtin University Human Research Ethics Committee (approval number HR110/2014), and the Catholic Education Offices and Departments of Education in Western Australia, Victoria, Queensland, New South Wales, Tasmania and South Australia. Written informed consent will be obtained from all adult participants. Participants under 18 years of age will provide informed written assent, and their parents will provide informed written consent for their participation. Principals of the schools attended by participants in the intervention group will provide informed written approval for their staff to use the BOOST-A™; consent is not required by this group because the teachers are not taking part in data collection. Participants in the control group will be offered the opportunity to use the BOOST-A™ once the trial is complete, if it is proven to be effective in achieving the trial objectives.

The trial design and procedures will adhere to the National Statement on Ethical Conduct in Human Research [71] and the Australian Code for the Responsible Conduct of Research [72]. The trial is registered with the Australia and New Zealand Clinical Trial Registry (#ACTRN12615000119594). The trial was developed according to the Consolidated Standards of Reporting Trials (CONSORT) 2010 guidelines [73].

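### The protocol claims participant blinding, and self-report free of assessor bias, but intervention families knowingly use a named programme and rate their own outcomes

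*Protocol article*

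**What the plan says.** All references are to the protocol article.

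- **Treatment allocation** asserts blinding and concedes two other sources of bias: "Participants will be blinded to their treatment; however, non-blinded allocation and lack of randomization could introduce potential bias". It explains that the intervention arm's forms differ from the control arm's, "as they will contain information about the BOOST-A™, to ensure blinding to treatment is maintained". It also says that parents and professionals outside the research team administer the programme, and that school staff are involved.
- **The intervention: BOOST-A** describes access: "The BOOST-A™ is delivered in four online modules with an introduction via a website that requires a login". Table 1 has the adolescent and parents working on the introduction and the first two modules at home, then meeting with a team.
- **Trial design and procedures** says: "Participants in the intervention group will complete the BOOST-A™ at home and/or at school". The period is 12 months, with an initial team meeting and at least one review meeting. Controls follow their school's existing planning process.
- **Outcome measures** says: "The outcome measures are all self-report, eliminating the risk of assessor bias". The abstract names adolescents and their parents as the people who complete the questionnaires.

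**The concern.** Two assurances about bias appear in the text, and the described procedures do not deliver either as worded. People who are told about a programme, log in to it and convene meetings around it know that they are receiving it. The same people then answer questionnaires about self-determination, support, career planning and wellbeing. Expectation, or a wish to report progress, can move such answers with no change in the underlying construct.

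The article intends the trial to give evidence of effectiveness. A reader who accepts the blinding and assessor-bias statements would credit a positive result with protection that it lacks. An open-label comparison with regular practice is a legitimate design. The fault lies in describing it as something else.

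**Working it through.** **Step 1. Who knows what.** The plan gives no figure for blinding, so the sections are set side by side.

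| Group | What they receive or do | Can they be blind to their own treatment? |
|---|---|---|
| Intervention adolescents | Form describing BOOST-A; login; four modules; team meetings | No |
| Intervention parents | Same form; take part in every module; help administer the programme | No |
| School staff in the intervention arm | Involved in administering it; principals approve its use (Ethics, consent and permissions) | No |
| Controls | Usual school planning; form without the BOOST-A description | They know they have usual planning; they might not know of the programme |

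Only the last row leaves room for concealment, and it is narrow. The inclusion criteria include computer skills sufficient to use the online BOOST-A, and Identification and recruitment says the flyer outlines the inclusion criteria. A control family that read the flyer may have seen the programme named. That section also has the information form sent at initial contact, whereas Treatment allocation has it sent after allocation, so what controls have seen, and when, is not settled.

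**Step 2. Who assesses.** The outcome measures are self-report. The primary measure, the AIR, covers the adolescent's own perceptions and the opportunities they see at home and school. In the intervention arm the assessor is therefore a person who knows what was received. Of the secondary scales, the TPOS is closest to the programme. The programme's developer wrote it, and each of its 16 items addresses one of the Fig. 1 objectives on which the programme was built. The adapted LCQ asks about support from the team, and Module 2 helps the adolescent form that team.

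**Step 3. Is it dealt with elsewhere?** Treatment allocation concedes bias from non-blinded allocation and non-randomization only. The caution about the TPOS under Secondary outcome measures concerns its unknown validity and reliability. Neither covers rating by respondents who know their treatment.

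**Step 4. Illustration of size.** The document gives no size for the bias, so the shift *b* is assumed. It is in SD units of the quantity compared between arms, with a true effect of zero and independent participants (school clustering ignored). The stated 40 per group (Sample size) and α = .05 are used, taken as two-sided.

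The noncentrality is δ = b × √(n/2) = b × √20 = 4.472b, with 2 × 40 − 2 = 78 degrees of freedom. The probability of p < .05 is the noncentral *t* probability beyond the two-sided critical value.

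| Assumed shift b (SD) | δ | P(two-sided p < .05) |
|---|---|---|
| 0 | 0 | 5% |
| 0.1 | 0.45 | 7% |
| 0.2 | 0.89 | 14% |
| 0.3 | 1.34 | 26% |
| 0.4 | 1.79 | 42% |
| 0.5 | 2.24 | 60% |

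The planned total of 80 does not reproduce under the two-sided formula for d = 0.6 and 80% power: 2 × (1.960 + 0.842)² / 0.6² = 43.6, so 44 per arm and 88 in total. That is a separate matter; here 40 per arm is only the stated input.

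**The case against.** The best defence has three parts.

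1. **The forms.** They may be meant to hide the programme, or the comparison, from controls. That is plausible and would be a real, if partial, safeguard, so a reader should not infer that no one in the trial could be unaware of anything. But the text claims blinding of participants to their treatment, which is wider, and the flyer makes even the narrow version uncertain.
2. **Assessor bias.** If an assessor means a researcher who scores participants, there is none, and the sentence is true in that sense. This stands. What it leaves out is that the risk passes to the respondent.
3. **Candour.** The article does warn of potential bias and does promise caution with the TPOS. It nowhere says that results are protected from expectation effects; a reader could draw that only from the two assurances.

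Three stronger readings are tempting but unsupported. The offer of BOOST-A to controls does not show that they were unblinded during the trial: it applies after completion and only if the programme proves effective, and the document does not say when controls are told. No one value of the bias, such as 0.2 SD, can be taken as likely, because nothing in the document points to one. The lack of a statement on masking the analyst is not an error either, since the article makes no claim about it and such detail commonly sits in a fuller document.

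**Conclusion.** The statement that participants are blinded to their treatment is wrong for the intervention arm, and the arm-specific forms cannot make it right. The statement on assessor bias holds only in the narrow sense that no researcher rates outcomes. Response bias remains possible for the AIR and for the secondary scales, most plainly the TPOS, and the article does not acknowledge it.

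This conclusion rests on the text alone. The 7% to 60% range depends wholly on the assumed shifts and on the simplifications stated with it. It shows only that a modest shift would matter at this sample size, not that one will occur. The point should be corrected; it does not make the trial unsound.

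**What to change.** - In Treatment allocation, replace "Participants will be blinded to their treatment; however, non-blinded allocation and lack of randomization could introduce potential bias" with a statement that the trial is open-label for intervention adolescents, parents and school staff. Keep the admission about allocation and non-randomization.
- Replace "to ensure blinding to treatment is maintained". If the aim is to keep controls unaware of the programme, say exactly that and no more, and make it agree with the flyer, the inclusion criteria and the stated timing of the forms.
- In Outcome measures, replace "The outcome measures are all self-report, eliminating the risk of assessor bias" with a statement that no researcher rates outcomes, but that intervention respondents know what they received, so response bias is possible.
- State as a limitation that effects on self-reported outcomes may include response bias, particularly for the TPOS, and word the effectiveness conclusion accordingly.

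The cost is a few sentences. No new data, participants or analyses are needed, and the change can still be made although follow-up collection has begun. The trial's stated protection against bias becomes less favourable, as the design requires.

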##### Sample size

Altman’s nomogram equation was used to determine the sample size. A total sample of n = 80 (n = 40 in each group) would be the minimum required to identify a standardized difference of 0.6 (i.e., Cohen’s *d*) [53], with a power of 80% and a critical alpha value of .05.

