##### Statistical analysis

Simple descriptive statistics (frequencies and percentages for categorical variables; means, standard deviations, ranges for continuous variables) will be used to summarize the demographic and baseline profiles of participants. These baseline variables will include the assessment of autism severity (using the SRS-2), and the outcome measures described above. The Chi square or *t* test (as appropriate) will be used to compare the profiles of participants between the intervention and control groups. If any continuous data are found to be not normally distributed (from the Kolmogorov–Smirnov test), these data may either be transformed to improve their normality or analyzed using an appropriate non-parametric test.

Effectiveness of the intervention for the AIR, the primary outcome, will be determined by calculating the change from Time point 1 to Time point 2, and comparing the changes within and between intervention and control groups using dependent and independent *t* tests (or non-parametric Wilcoxon signed rank tests and Mann–Whitney U test if the data are not normally distributed). If the analysis reveals differences in baseline characteristics between the intervention and control groups, the analyses will be adjusted for these differences using a general linear model (GLM). Analysis of secondary outcomes will be performed using a multivariate ANOVA (MANOVA). Analyses will be performed using an intention-to-treat strategy, where participants will be classified as belonging to the group (intervention or control) to which they were initially allocated, regardless of the treatment they actually received. Participants who do not provide outcome data at Time point 2 will still be included in the trial, and their Time point 1 data will be used for Time point 2 to allow for intention-to-treat analysis of the data. The Statistical Package for the Social Sciences (SPSS v.22) will be used to analyze the data, and a p value of .05 will be used as the level of statistical significance in all inferential analyses.

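### Eighty participants is not the minimum for d = 0.6 at 80% power: a two-sided test needs 88 to 90, and 40 per group gives about 75%

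*Protocol article*

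**What the plan says.** The Sample size section reports the method, "Altman’s nomogram equation was used to determine the sample size", and the result: a total of 80, with 40 "in each group) would be the minimum required to identify a standardized difference of 0.6". The target difference is glossed as Cohen's d, "with a power of 80% and a critical alpha value of .05". Neither the sidedness of the test nor the SD used for standardizing is given.

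Trial design and procedures describes the design: "The trial will be a cluster group, two-arm, superiority trial with 1:1 allocation ratio". It also says: "The trial will aim to detect any difference in these outcomes between participants in the intervention group" and the control group.

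Statistical analysis sets the primary analysis of the AIR as change from Time point 1 to Time point 2, "comparing the changes within and between intervention and control groups using dependent and independent" t tests, with rank-based tests if the data are not normal. A participant without Time point 2 data stays in the analysis, with the Time point 1 value used again.

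**The concern.** All the inputs to a standard two-group calculation except sidedness are printed, so the result can be checked, and it does not follow from them. The article calls 80 a minimum, which is a precise claim.

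Power tells a reader how to weigh a null result on the primary outcome. The stated design implies a 20% chance of missing a true difference of 0.6. On the same inputs, two-sided and with 0.6 on the analysed scale, that chance is about 25%. Readers would then take a null result as somewhat stronger evidence against such an effect than the design supports.

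**Working it through.** **Inputs.** From Sample size: d = 0.6 (so SD = 1 on the standardized scale), alpha .05, power 80%, 40 per group. From Trial design and procedures: two arms, 1:1. From Statistical analysis: independent t test between groups. Assumed: a two-sided test, which fits the aim of detecting any difference. One-sided is tried as well.

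**Attempt to reproduce 80, two-sided.** The normal formula is n per group = 2(z₁₋α/₂ + z₁₋β)² / d².
- n = 2 × (1.960 + 0.842)² / 0.36 = 43.6, rounded up to 44 per group, 88 in total (unrounded total 87.2).
- Exact noncentral t: 44 per group gives 79.5% power and 45 gives 80.4%, so 45 per group, 90 in total.

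**One-sided.**
- Normal: 2 × (1.645 + 0.842)² / 0.36 = 34.4, so 35 per group, 70 in total.
- Exact t: 36 per group, 72 in total.

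No version gives 80.

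**Power with 40 per group, d = 0.6.** The noncentrality is 0.6 × √(40/2) = 2.683.
- Two-sided, normal: Φ(2.683 − 1.960) = 76.5%. Exact t: 75.5%.
- One-sided, normal: Φ(2.683 − 1.645) = 85.0%. Exact t: 84.5%.

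**Difference detectable with 80% power, 40 per group, two-sided.**
- Normal: (1.960 + 0.842) × √(2/40) = 0.626. Exact t: 0.634.
- Putting d = 0.63 into the normal formula returns 80 in total, so the stated size fits 0.63 rather than 0.6.

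**Effect of the undefined SD.** Suppose 0.6 is in SDs of the AIR score itself, with equal SDs at both time points and correlation r between them. The SD of change is then √(2(1 − r)) score SDs, and the effect on the change scale is 0.6 / √(2(1 − r)). Two-sided exact-t power with 40 per group:

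| r | effect on change scale | power |
|---|---|---|
| .40 | 0.548 | 68% |
| .50 | 0.600 | 75.5% |
| .56 | 0.640 | 80.6% |
| .60 | 0.671 | 84% |
| .74 | 0.832 | 96% |

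The .74 is the three-month test–retest value quoted under Primary outcome measure. The article gives no 12-month correlation.

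**Missing follow-up under the planned carry-forward (illustration; rates assumed).** A fraction p of each group is entered with zero change. Take a mean change of 0 in controls and 0.6 in the intervention group, with SD 1. The mean difference becomes 0.6(1 − p), and the variances become (1 − p) + 0.36p(1 − p) in the intervention group and (1 − p) in controls.
- p = 10%: difference 0.54, variances 0.9324 and 0.90, d = 0.54 / √0.9162 = 0.564, power about 70%.
- p = 20%: difference 0.48, variances 0.8576 and 0.80, d = 0.48 / √0.8288 = 0.527, power about 64%.

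**The case against.** Four arguments can be made for the plan.

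*The gap is small, and a nomogram is read off a graph.* True: it is 8 to 10 participants, and 0.60 against 0.63 is a fine distinction when 0.6 itself is given no derivation. This may explain the figure. It does not make 80 a minimum, particularly as the article refers to an equation.

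*Sidedness is not stated.* This does not rescue the figure, because a one-sided test needs only 70 to 72.

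*The primary test is on change scores, which may be more precise.* This stands in part. A reader might infer from the shortfall that a 25% risk of missing the effect is the best case, or that only a one-sided test could reach 80% power. The article supports neither. If 0.6 is in raw-score SDs and the 12-month correlation is about .56 or more, the change-score test reaches 80%. Below .5 its power is under 75.5%. Because neither the scale nor the correlation is given, this route shows neither adequate power nor a worse shortfall.

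*Attrition and clustering belong in the full protocol.* Also fair. A reader might go on to infer a 35% to 40% risk of missing the effect once losses and school clustering are added. That would require an assumed loss rate stacked on an assumed design effect, and the article gives neither. Removing non-responders from the count would also misrepresent the plan, which keeps them by carrying baseline values forward. Same-school allocation is described as an exception within individual recruitment across Australia, so many schools may contribute one participant.

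**Conclusion.** The concern holds as an arithmetic error in the Sample size section. For a two-sided test at alpha .05 and d = 0.6 on the analysed scale, 80% power needs 88 to 90 participants. The stated 80 gives about 75%, or 80% for d of about 0.63. Two-sidedness is an assumption, though the conclusion that 80 is not the minimum holds for a one-sided test too. The shortfall of 4 to 5 points also assumes that 0.6 is in SDs of the quantity tested; on the raw-score scale, power could lie on either side of 80%. Any loss to follow-up or within-school correlation would lower power further, by amounts the article does not allow one to fix. The error changes no outcome, test or decision rule.

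**What to change.** Reword the Sample size section, with no change to enrolment:

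- State that 80 analysed participants (40 per group) give about 75% power for d = 0.6, or 80% power for d of about 0.63, with a two-sided test at alpha .05.
- Delete the claim that 80 is the minimum required.
- State whether 0.6 is in SDs of the AIR score or of its change. If it is the score, give the assumed 12-month correlation and the resulting change-score power.
- Optionally, and labelled as assumptions, add that under the carry-forward rule 10% or 20% missing follow-up would lower power to about 70% or 64% with no mean change in controls, and that any within-school correlation would lower it further.

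Baseline adjustment should not be cited as making up the shortfall, because Statistical analysis adjusts only if baseline characteristics differ between groups. That argument would be available only if adjustment were made unconditional, which is a change to the analysis and not just to the wording.

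The cost is one paragraph and a less favourable stated power.
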